### Statistical Analysis

#### Overview

The GLAD project and the following methods have been prospectively registered on the Open Science Framework [21]. The methods outlined herewith are based on the most up-to-date definitions used by the GBD, at the time of writing this protocol. Given that the GBD is subject to change, future iterations may vary in accordance with such amendments. The initial iteration of the GLAD project will focus on dietary exposures, and the methods described within this protocol refer specifically to this first iteration. Subsequent updates to the protocol may be made when additional lifestyle risk factors are considered in future iterations of the GLAD project.

#### Exposure and Outcome Definitions

Definitions of dietary intakes and CMDs are based on definitions used by the GBD [1,18]. In addition to the 15 dietary intakes used by the GBD, ultraprocessed food intake will be included where practicable given the increasing literature in the field linking this dietary exposure to a wide range of health outcomes [22-25]. In doing so, we will use the most widely adopted food classification system based on the purpose and extent of industrial food processing, Nova, to define ultraprocessed foods [20]. Furthermore, we will follow best practice guidelines when categorizing foods according to the Nova food classification system [26].

CMDs can be measured differently across epidemiological studies. They are most commonly assessed using self-reported symptom scales with cutoffs for diagnosis, from medical records, or using diagnostic interviews. Multimedia Appendix 1 outlines some commonly used tools and their recommended cutoffs for identifying symptoms of depression and anxiety. The sensitivity, specificity, and diagnostic accuracy of these tools largely depend on the population. When undertaking meta-analyses, we may conduct a sensitivity analysis to determine if the magnitudes of associations change based on exposure and outcome measurement or ascertainment type.

#### Covariates and Confounders

To address the anticipated heterogeneity of member studies’ available data, a set of core confounders are provided for the purpose of generating a consistent minimally adjusted analysis. The conduct of additional analyses (eg, using additional variables, fitting sensitivity models, or exploratory analyses) is at the discretion of the study author or authors based on available data and reviewer requests when studies are submitted for publication.

To be included in the GLAD project, member studies must adhere to the iteratively adjusted models (Textbox 1).

The iteratively adjusted statistical models required for the Global burden of disease Lifestyle And mental Disorders (GLAD) task force.Model 1: Unadjusted model, with the dietary variable (as listed in Table 2) as the exposure and depression or anxiety as the outcome.Model 2: Minimally adjusted model, with the dietary variable of interest, depression or anxiety, and with baseline mental disorder status (or lifetime history of mental disorders for cross-sectional studies), age, sex, and a measure of socioeconomic status, such as household income, employment status, or education.Sensitivity model: Same as model 2, but with adjustment for total energy intake.

Of particular relevance in nutritional epidemiology are methods for adjusting for energy intake. Intake of specific nutrients are correlated with total energy intake, and so appropriate adjustment is required to disentangle the effect of the nutrient from the effect of energy. For example, an individual may alter intake of a specific nutrient by changing dietary composition, and not by changing total energy intake. As such, controlling energy intake can reduce confounding, and failure to appropriately control for total energy intake may nullify associations between nutrient intake and disease outcomes [27]. Given the correlation between nutrient intake and energy, the application of Willett’s residual method is recommended to account for total energy intake [27]. This involves fitting a regression model with the dietary variable as the outcome and total energy intake as the exposure, predicting residuals from this model, and then using these predicted residuals in the analysis models [27].

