**Figure 1 figure1:**
[figure not shown]
The GLAD taskforce composition and responsibilities within the GLAD project. GLAD: Global burden of disease Lifestyle And mental Disorders.

To identify potential member studies for participation in the GLAD project, which would apply the harmonized data analysis protocol to their own datasets and contribute their results to the broader initiative, we used a multistep process. The first step was to identify epidemiological studies that had the necessary variables by which the study lead or representative could execute our analysis plan (eg, food frequency questionnaires from which to derive GBD-defined dietary risks combined with mental health questionnaires to identify cases of depression or anxiety). This process involved a literature search to identify potentially eligible studies and key contacts to approach for invitation to participate in the GLAD project. To operationalize the dietary risk variables, we used previous GBD papers, which contained the definitions of each dietary exposure (Table 1) and depression and anxiety (Table 2) [1,19]. In addition to using the literature to identify potentially eligible datasets, we also drew on previous collaborations of the GLAD project team and researchers in the field of nutritional psychiatry (eg, via the International Society of Nutritional Psychiatric Research), as well as promoting the project on Food and Mood Center social media sites. Data custodians of identified studies were contacted, and those with relevant data and who had the capacity to participate in the GLAD project completed an expression of interest via the Food and Mood Center website.

To be eligible for inclusion, member studies must have dietary intake (Table 1) and depression and anxiety outcomes (Table 2) consistent with GBD definitions, or the ability to recode existing variables accordingly. Any deviations to these definitions must be reported and will be accounted for accordingly as reported below in “Future Directions: Meta-analyses.” Any study design, in any location, with any sample size, is eligible to be a member study and can complete the required data analysis.

**Table 1 table1:** Dietary exposure definitions and required coding for the GLAD project^a^.

Dietary risk factor	GBD^b^ exposure definition	Required coding^c^

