Ultra-processed foods (optional)	Any intake of ultraprocessed foods, as defined by the Nova system as any food item in Nova category 4 (“ultraprocessed food”), in grams [20].	grams/day

^a^Based on the GBD (Global Burden of Diseases, Injuries, and Risk Factors Study) risk exposure definitions (Pages 217-218 in Supplementary Appendix 1 in the study by the the GBD 2019 Risk Factors Collaborators [19]).

^b^GBD: Global Burden of Diseases, Injuries, and Risk Factors Study.

^c^Analyses using continuous exposures are required by the GLAD Taskforce. The units listed here are recommended, however, these may be rescaled to more meaningful units in papers (eg, per 10 g) provided the original units are available to the project team.

**Table 2 table2:** Mental health definitions and recommended coding for the GLAD^a^ project^b^.

Mental disorder	Outcome definition	Diagnostic reference	Recommended coding^c^
Major depressive disorder	Involves the presence of at least one major depressive episode, which is the experience of either depressed mood or loss of interest/pleasure, for most of every day, for at least two weeks.	DSM-IV-TR^d^: 296.21–24; 296.31–34. ICD-10^e^: F32.0-9; F33.0-9.	0=no MDD^f^; 1= MDD
Anxiety disorders (any subtype)	Involves experiences of intense fear and distress, typically in combination with other physiological symptoms. Anxiety disorders will be modeled as a single cause for “any” anxiety disorder to avoid the double-counting of individuals meeting criteria for more than one anxiety disorder. Epidemiological estimates reporting an outcome for “any” or “total” anxiety disorders will be included if they reported on at least three anxiety disorders.	DSM-IV-TR: 300.0-300.3; 208.3; 309.21; 309.81. ICD-10: F40-42; F43.0; F43.1; F93.0-93.2; F93.8.	0=no anxiety disorder; 1=anxiety disorder

^a^GLAD: Global burden of disease Lifestyle And mental Disorders.

^b^The definitions and diagnostic references presented in this table are the current definitions used by the GBD (Page 4 in the Supplementary Appendix in the study by the GBD 2019 Mental Disorders Collaborators [1]). Since GLAD members may use alternative methods to ascertain disorder status, definitions or diagnostic references may vary slightly. For example, somatic forms of depression may be captured more by symptom scales, or studies using prescriptions may use Anatomical Therapeutic Chemical codes to determine incident depression and anxiety.

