^c^Outcomes must be binary (condition present vs condition absent). For studies that only use symptom scales, validated cutoffs can be used to determine condition present versus condition absent (refer to Multimedia Appendix 1).

^d^*DSM-IV-TR*: *Diagnostic and Statistical Manual of Mental Disorders (Fourth Edition, Text Revision)*.

^e^*ICD-10*: *International Statistical Classification of Diseases, Tenth Revision*.

^f^MDD: major depressive disorder.

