## Results

As of August 2024, 18 longitudinal studies have agreed to participate in the GLAD project (Table 3). These studies have sample sizes ranging from 639 participants to 171,000 participants (Table 4).

The GLAD project comprises 3 essential phases, which will be repeated for other lifestyle exposures of interest: (1) conducting a systematic search to identify relevant studies and recruit study leads to contribute data, (2) generating estimates of study-level associations of dietary risk factors with CMDs using harmonized data analysis protocols developed by the GLAD Taskforce and approved by the GBD, and (3) pooling results from each study to provide the GBD with robust estimates to calculate the diet-CMD risk-outcome pairs in the first instance.

As of August 2024, phase 1 of the GLAD project has been completed, and phase 2 is due for completion in early 2025, at which time phase 3 of the GLAD project is due to begin (Figure 3).

Phase 1 includes searching for and recruiting studies with suitable data, harmonizing data definitions by ensuring member studies use the exposure definitions listed in Table 1 and the outcome definitions listed in Table 2, and harmonizing data analyses by ensuring member studies follow the statistical analysis plan presented in this paper.

**Table 3 table3:** Details of the ethics approval for currently listed member studies^a^.

Study name	Ethics review board
The African-PREDICT^b^ study [44]	North West Department of Health and Health Research Ethics Committee of the North-West University.
Child to Adult Transition Study [45]	Royal Children’s Hospital Human Research Ethics Committee.
Dunedin Study [46]	Health and Disability Ethics Committee, Ministry of Health.
Environmental Risk (E-Risk) Longitudinal Twin Study [47,48]	Joint South London and Maudsley and the Institute of Psychiatry Research Ethics Committee.
Fragility in the Elderly Lombardy Study [49]	Ethics committee of the University of Pavia.
Geelong Osteoporosis Study [50]	Barwon Health Human Research Ethics Committee.
Health4Life [51,52]	University of Sydney, NSW^c^ Department of Education, University of Queensland, Curtin University, and relevant Catholic school ethics committees.
Healthy Life in an Urban Setting [53]	Ethical Review Board of the Academic Medical Center Amsterdam.
Longitudinal Aging Study Amsterdam [54]	Medical ethics committee of the VU University Medical Center.

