### Strengths and Limitations

Currently, the GBD is unable to include lifestyle exposures such as dietary intake as a risk for CMDs due to the following: difficulties determining directionality and causality, inconsistency in dietary variables and methods, small sample sizes, and lack of global representation. A strength of the GLAD project is that it will address all these methodological considerations. We will (1) prioritize prospective studies using incident cases (ie, excluding those with baseline CMDs) to obtain risks of CMDs attributable to dietary intake, and not the other way around (to determine directionality or temporality), (2) include all study designs (including from experimental or randomized controlled trials to strengthen causal conclusions), (3) conduct harmonized data analyses approved by the GBD (to improve consistency between studies and specificity of the diet-CMD relationship), and (4) pool data from multiple studies from around the world (to address sample size and global representation).

Despite the clear strengths of the GLAD project, there are some limitations. First, the GBD study is an ongoing and dynamic study, and definitions and methods are constantly evolving. Every effort will be made to ensure the taskforce are following GBD-approved methods, however, some changes from the GBD may be unavoidable. Second, since the GBD does not currently include ultraprocessed food as a dietary risk factor, the definitions and methods used by the task force may not reflect those used in future iterations of the GBD. Finally, although food intakes provide a general overview of diet quality, people do not eat food items in isolation. The current methods used by the GBD do not currently consider dietary patterns. This may limit interpretations to specific food items and not to an overall dietary pattern.

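### Model 2 makes cross-sectional studies adjust for lifetime history of mental disorder without excluding the current episode; where history includes it, the diet odds ratio compares current with remitted illness

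*Protocol article*

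**What the plan says.** Under Covariates and Confounders, the Protocol article sets the condition for inclusion: "member studies must adhere to the iteratively adjusted models (Textbox 1". Model 2 in that textbox adjusts for baseline mental disorder status, age, sex and a socioeconomic measure. For designs without a baseline, the first of these is replaced: "or lifetime history of mental disorders for cross-sectional studies". The text does not say whether this history stops before the current episode or which disorders count.

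Four other places bear on the point.

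- **Eligibility (Methods, Recruitment):** "Any study design, in any location, with any sample size, is eligible to be a member study and can complete the required data analysis".
- **Outcome (Table 2):** the depression entry reads "Involves the presence of at least one major depressive episode" and gives no time window. Footnote c adds that, for studies with symptom scales only, "validated cutoffs can be used to determine condition present versus condition absent".
- **Effect measure (Estimating Risk Ratios, Odds Ratios, and Hazards Ratios):** the primary risk ratio needs diet at baseline, a later outcome, and exclusion of people already ill. A study that cannot supply this uses ordinary logistic regression.
- **Membership (Results):** "As of August 2024, 18 longitudinal studies have agreed to participate in the GLAD project". A note under Table 3 says that further studies may be taking part without being listed.

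**The concern.** Baseline status in a cohort is fixed before the outcome occurs. Its cross-sectional substitute need not be. Read literally, a lifetime history includes an illness that is present now, so the covariate can contain the outcome it is meant to adjust for.

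People who have never been ill then contribute nothing to the diet estimate. What remains is whether diet differs between those ill now and those recovered. That is a question about persistence, whereas the project wants the association of diet with having or developing the disorder. Because Table 2 gives depression no time window, a study could even place the same lifetime variable on both sides of the model.

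The risk is that a cross-sectional study follows Textbox 1 exactly and supplies an adjusted OR that looks ordinary but answers another question.

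**Working it through.** The article states no effect size, prevalence or sample-size target for this analysis, so there is no figure of its own to reproduce. The check is algebra followed by simulation.

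**Algebra.** Let Y be current disorder, x diet and H lifetime history. Omitting the other covariates, Model 2 is

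logit P(Y = 1) = a + b·x + g·H.

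Suppose H includes the current episode. Then Y = 1 implies H = 1, and everyone with H = 0 has Y = 0. The likelihood rises as a goes to minus infinity while a + g stays fixed at some value c. In the limit the H = 0 group contributes a factor of 1, and what is left is the likelihood of logit P(Y = 1) = c + b·x among people with H = 1. So g has no finite estimate, while b does: it is the log OR for current versus remitted illness.

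**Simulation inputs (all assumptions, none from the article).** N = 400,000; diet standard normal; lifetime prevalence 20%; 30% of lifetime cases current, so current prevalence is about 0.20 × 0.30 = 6%; diet OR 1.3 per SD on onset, persistence or both, or 1.3 on onset and 1/1.3 on persistence. Age, sex and socioeconomic status are left out.

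**(a) History includes the current episode.** In every run there were 0 cases with H = 0. The history coefficient was 25.7 with SE of about 627 to 630.

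| Diet acts on | OR without history | OR with history | OR among H = 1 only |
|---|---|---|---|
| Onset only | 1.239 | 0.998 | 0.998 |
| Onset and persistence | 1.504 | 1.302 | 1.302 |
| Persistence only | 1.208 | 1.296 | 1.296 |
| Opposite directions | 1.029 | 0.766 | 0.766 |

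The last two columns agree, as the algebra requires. The diet estimates have SEs near 0.008 on the log scale, so they look well behaved.

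**(b) Outcome and covariate are the same lifetime variable.** Separation is complete. The diet coefficient is about 0 with SE 567, so it is not estimable.

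**(c) Symptom-scale outcome, history recorded separately.** Assumed scale sensitivity is 0.85 and specificity 0.90; history sensitivity is 0.60 and specificity 0.95. About 41,000 of 58,000 scale-positive people had no recorded history, so nothing separates. The OR moves as follows:

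- onset only: 1.081 to 1.053. On the log scale, 0.078 to 0.052, a loss of about one third;
- onset and persistence: 1.161 to 1.134. On the log scale, 0.149 to 0.126, a loss of about 16%;
- persistence only: 1.063 to 1.064;
- opposite directions: 1.003 to 0.976.

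**(d) History strictly before the current episode.** Assumed prior history is 15%, current prevalence 7%, history OR 4 and conditional diet OR 1.30. There were 17,144 cases without prior history and no separation. Model 2 returned 1.304 (unadjusted 1.379), which recovers the value built in. The fault therefore lies in the open timing of the covariate.

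**The case against.** **The term can be read as prior history.** It stands in for baseline status, and an analyst might take it that way. The article nowhere says that the covariate includes the current episode. This stands, and it is why the point is conditional. But nothing in Textbox 1 or Table 2 steers a study to the harmless reading, and an ever-diagnosed item satisfies the wording.

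**Symptom scales are described as among the most common outcome measures, and with them nesting need not occur.** This also stands. In that setting the effect is modest, as case (c) shows.

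**The article allows another approach when model assumptions fail.** In part. A separation warning on the history term might prompt a careful analyst. The diet OR itself stays finite and plausible, however, and no replacement is named for a required model.

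**Two stronger readings are tempting, and the documents support neither.**

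- A reader might infer that the adjusted OR is always driven to 1 or that the model fails. Under nesting only the history coefficient separates, and the diet OR can lie below, at or above 1. It goes to 1 when diet is assumed to have no effect on persistence, which is an assumption and not a finding.
- A reader might infer that such ORs will distort the pooled estimates given to the GBD. The Future Directions section leaves pooling to a separate protocol and foresees meta-regression, cross-walking and sensitivity analyses. Strengths and Limitations says the project will "prioritize prospective studies using incident cases (ie, excluding those with baseline CMDs". How cross-sectional ORs enter the synthesis is not settled here.

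**Conclusion.** The point holds in conditional form. A required rule, followed literally, lets the adjustment variable contain the outcome. Where it does, Model 2 no longer estimates the diet-disorder association. The direction of the error is not fixed: under the assumed rates, 1.239 fell to 0.998, 1.208 rose to 1.296, and 1.029 fell to 0.766. Where outcome and history are the same lifetime variable, there is no estimate at all.

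These sizes rest on the assumed prevalences, the diet effect of 1.3 per SD and perfect nesting. The structural result, that people without history drop out, does not depend on those rates; it needs only nesting.

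Reach is limited. All 18 listed studies are longitudinal, and the primary incident risk ratio is untouched. The clause is still live: any design is eligible, unlisted studies may take part, and the authors wrote wording specifically for cross-sectional studies. It should be corrected, but it is not a critical fault.

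**What to change.** In Textbox 1, define the cross-sectional covariate as depression or anxiety episodes that ended before the current episode. Add that a study unable to date past episodes omits the term and reports that it did so. This settles both the timing and the disorders counted, and it removes the case in which outcome and covariate are the same variable.

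The cost is one or two sentences. The downside is that studies without dated episodes lose adjustment for prior disorder, so their Model 2 would be less comparable with the others; reporting the omission lets the later synthesis take account of it. The place of cross-sectional ORs in the meta-analysis can be left to the phase 3 protocol.

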#### Estimating Risk Ratios, Odds Ratios, and Hazards Ratios

Each study is required to use risk ratios (estimated by Poisson regression with robust SE) as the primary means of assessing the association of dietary intake with CMDs. Risk ratios are based on incident cases, and so models will need to exclude participants with depression or anxiety at baseline. Furthermore, to determine incident risk, studies must have dietary exposures at baseline and depression, or anxiety measured at a subsequent time point. Where the estimation of a risk ratio is not possible (refer to Figure 2), for example, where the total number of people exposed at baseline is not available (such as for retrospective or case-control studies) [29], odds ratios are estimated using standard logistic regression techniques. Where only time-to-event data are available, hazard ratios are used, estimated by a Cox proportional hazards model. For rigor, all effect estimates will be accompanied by a 95% CI and exact *P* value [30].

Models can be fitted using any statistical analysis software, including R (R Core Team), SAS/STAT (SAS Institute Inc), Stata (StataCorp LLC), and SPSS (IBM Corp). Before fitting the relevant models, Member studies must assess model assumptions. Should any model assumptions be violated, an alternate approach to analysis may be selected. For example, the nonlinearity of continuous variables should be investigated, and transformations or nonlinear models fitted where necessary. Similarly, should any of the assumptions of Cox proportional hazards models be violated, alternative strategies will be deployed to account for these violations.

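### The recommended energy-residual step does not say that total energy stays in the outcome model; if it is left out, energy adjustment may be incomplete and member studies' sensitivity estimates may differ

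*Protocol article*

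**What the plan says.** Textbox 1 (Covariates and Confounders) defines the third required model as "Sensitivity model: Same as model 2, but with adjustment for total energy intake". Model 2 contains the dietary variable, baseline mental disorder status, "age, sex, and a measure of socioeconomic status, such as household income, employment status, or education".

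The text after Textbox 1 says how energy should be handled: "the application of Willett’s residual method is recommended to account for total energy intake". It describes the method as "fitting a regression model with the dietary variable as the outcome and total energy intake as the exposure", then "predicting residuals from this model, and then using these predicted residuals in the analysis models". No other first-stage covariate is named. The text neither says that energy is also a term in the outcome model nor rules it out.

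The section on estimating ratios makes "risk ratios (estimated by Poisson regression with robust SE) as the primary means" of assessing association, with logistic or Cox regression where a risk ratio cannot be obtained. It also asks that "the nonlinearity of continuous variables should be investigated, and transformations or nonlinear models fitted where necessary". Footnote c to Table 1 adds: "Analyses using continuous exposures are required by the GLAD Taskforce".

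**The concern.** A residual from a regression on energy alone is uncorrelated with energy in the whole sample. The outcome model, however, conditions on sex, age, socioeconomic status and baseline disorder status. Within levels of these, the residual can still be correlated with energy. If men and women eat different amounts of a food at equal energy, for example, the pooled slope differs from the within-sex slope. If energy is then absent from the outcome model, some energy confounding returns.

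Two things are at stake. First, this is the only required model that deals with energy, and the article itself says appropriate energy control is needed to separate a nutrient from energy. Second, three implementations fit the text: energy as a covariate, the residual alone, or both. The first and third give the same coefficient. The second in general does not, yet all three would be reported as the same sensitivity model in a project built on harmonized estimates.

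**Working it through.** The article states no figure on this point, so there is nothing to reproduce. The structure of the models comes from the article. Every correlation and effect size below is an assumption.

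**1. With energy kept, the residual method is exact.** Let X be intake, E energy, Z a Model 2 covariate, and R = X − a − bE the first-stage residual. Then βR + γE = βX + (γ − βb)E − βa. The models {R, E, Z} and {X, E, Z} are the same model rewritten, so the coefficient of R equals that of X. This holds for Poisson, logistic and Cox regression.

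**2. With energy left out.** R and E are uncorrelated overall, so the standardized coefficient of E on R given Z is

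k = −r(E,Z) · r(R,Z) / (1 − r(R,Z)²).

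The log RR per SD of R shifts by about kθ, where θ is the log RR per SD of energy with R held fixed.

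| r(E,Z) | r(R,Z) | k | Energy RR per SD | kθ | RR factor |
|---|---|---|---|---|---|
| 0 | 0.3 | 0 | any | 0 | 1.000 |
| 0.2 | 0.1 | −0.02/0.99 = −0.0202 | 1.1 | −0.0019 | 0.998 |
| 0.4 | 0.2 | −0.08/0.96 = −0.0833 | 1.2 | −0.0152 | 0.985 |
| 0.5 | 0.4 | −0.20/0.84 = −0.2381 | 1.2 | −0.0434 | 0.957 |
| 0.5 | 0.4 | −0.2381 | 1.5 | −0.0965 | 0.908 |
| 0.5 | 0.4 | −0.2381 | 2.0 | −0.165 | 0.848 |

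**3. Check by simulation.** Poisson models with robust SE, n = 400,000, one binary covariate, true log RR −0.10 per SD of residual. Entries are log RRs, and the SE of the residual-only estimates is about 0.006.

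| r(E,Z), r(R,Z), energy RR | Residual only | Residual + energy | Intake + energy | First stage on energy + covariate, no energy term | Intake, no energy |
|---|---|---|---|---|---|
| 0, 0.3, 1.2 | −0.1086 | −0.1087 | −0.1087 | −0.1086 | −0.0047 |
| 0.4, 0.2, 1.2 | −0.1142 | −0.0990 | −0.0990 | −0.0991 | −0.0269 |
| 0.5, 0.4, 1.2 | −0.1418 | −0.0971 | −0.0971 | −0.0974 | −0.0474 |
| 0.5, 0.4, 1.5 | −0.1954 | −0.0981 | −0.0981 | −0.0982 | −0.0013 |

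In the three correlated rows, residual-only differs from full adjustment by −0.0152, −0.0447 and −0.0973, in line with step 2.

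**4. Fiber example on a natural scale.** Assumed: equal numbers of men and women; energy 2000 kcal in women and 2500 in men, SD 500 within sex; fiber slope 0.008 g per kcal; residual SD 5 g; women eat d = 2, 4 or 6 g more fiber at equal energy; no true fiber effect; energy RR exp(g) per 500 kcal with g = 0.2.

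- var(E) = 500² + 250² = 312,500, and cov(sex, E) = 0.25 × 500 = 125.
- Pooled slope = 0.008 − d × 125/312,500 = 0.0072, 0.0064, 0.0056.
- Within-sex cov(R, E) = 0.0004d × 250,000 = 200, 400, 600.
- Within-sex var(R) = 25 + (0.0004d)² × 250,000 = 25.16, 25.64, 26.44.
- Bias in log RR per 10 g = (g/500) × 10 × cov/var = 0.159g, 0.312g, 0.454g.
- With no energy adjustment: cov = 0.008 × 250,000 = 2000, var = 25 + 0.008² × 250,000 = 41, bias = 0.976g.

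Residual-only therefore leaves 0.159/0.976 = 16%, 0.312/0.976 = 32% or 0.454/0.976 = 47% of the confounding. At g = 0.2 the null RR per 10 g is exp(0.032) = 1.03, exp(0.062) = 1.06 or exp(0.091) = 1.10, against exp(0.195) = 1.22 unadjusted. A Poisson simulation with n = 1,000,000 at d = 4 gave 1.067 for residual only, 1.001 for residual plus energy, 1.001 for intake plus energy, and 1.220 with no energy term.

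**5. Scale of the residual.** Least-squares residuals have mean zero. The negative share was 50% for symmetric intake, 62% to 69% for lognormal intake and 64% with 40% non-consumers. Adding a constant left the slope unchanged (−0.1142 before and after, in the second row of step 3).

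**The case against.** The strongest reply is that the text does not exclude an energy term. Textbox 1 says total energy is adjusted for, so a study entering residual plus energy complies with both statements and gets the exact answer. The article summarizes a named, cited method in a few lines, and the registered methods and the cited source are not at hand. The method is recommended rather than required, it serves a sensitivity model, and Models 1 and 2 are untouched. All of this stands. It limits the point to an incomplete specification whose literal reading can go wrong. It does not remove the point, because the article sets out the steps itself and nothing in them tells an analyst to keep energy.

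A reader might infer that the sensitivity model fails to adjust for energy. The article does not support that. In the fiber example residual-only still removes 84%, 68% or 53% of the confounding, and it removes all of it when the sexes do not differ in intake at equal energy. The 6 g case is also demanding, at 1.2 times the assumed 5 g residual SD, and 10 g is about two such SDs. Per SD, the null RRs for 2 g and 4 g are roughly 1.02 and 1.03.

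A reader might also infer that negative residuals corrupt the estimates. They do not bias a linear per-unit RR, OR or HR. They matter only for log or power transformations and for reading results against the intake levels in Table 1. Splines and polynomials accept negative values, and intake can be transformed before residualizing.

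Finally, a reader might conclude that harmonization is defeated. The meta-analysis outline foresees cross-walking or sensitivity analyses where analysis strategies differ, and exclusion of papers that depart substantially. That is partial protection, but it acts after the event and depends on each study reporting which route it took.

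**Conclusion.** The point holds as a gap in a stated procedure. Taken literally, with no energy term in the outcome model, the recommended steps may leave energy adjustment incomplete and can give a different estimate from the energy-as-covariate route that Textbox 1 equally allows.

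The shift is zero if the covariates are unrelated to energy or to the residual, or if energy does not predict the outcome. Over the assumed non-zero correlations, the RR factor per SD of residual runs from 0.998 to 0.848. In the assumed fiber example a null RR per 10 g becomes about 1.03 to 1.10. The article supplies none of the correlations or energy effects needed to say which case applies to any member study or food. The text should be changed because the correction is exact and nearly free. The primary analyses are not affected.

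**What to change.** In the Covariates and Confounders text and in the Textbox 1 sensitivity model, state that total energy intake is entered as a term together with the energy residual and the Model 2 covariates. The residual coefficient then equals the intake-plus-energy coefficient exactly, so the permitted routes agree.

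An alternative is to include the Model 2 covariates in the first-stage regression. In the simulated Poisson models this agreed with full adjustment to within 0.0003 on the log scale. Keeping energy in the outcome model is the simpler choice, because its agreement is exact for the logistic and Cox models too.

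As an optional wording note, the predicted intake at mean energy can be added back to each residual where a transformation or the Table 1 scale is needed. This does not change a linear slope.

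The cost is one sentence and one more parameter per model, using a variable that any study computing residuals already holds.
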